## 1.13 Comparator Vaccine

### 1.13.1 *Rationale for use of a comparator vaccine*

Having a comparator vaccine is particularly useful in phase 1 trials conducted in endemic areas, since background immunity and natural exposure to hookworm infection may otherwise make it difficult to interpret immunogenicity data. The use of a control group will permit comparison of immune responses between those vaccinated with *Na*-GST-1 and those not vaccinated with this antigen, and will result in a clearer interpretation of immunogenicity results. Although a placebo control group would accomplish the same goal, using a comparator vaccine that is beneficial to the participants increases the benefit-risk ratio, which is always relatively low in phase 1 trials.

Furthermore, the use of a comparator vaccine in a blinded study reduces potential investigator bias in reporting adverse events or attributing their causality. It will also safeguard against the probability that an excess of adverse events will be reported in this trial in comparison to an equivalent trial conducted in the United States. From prior experience conducting other trials at this study site, there will be many reported adverse events that are unrelated to the study

interventions: this rural population has reduced access to medical care and performs excessive heavy labour compared to an urban population or one living in the developed world. Thus, this population has significantly more medical afflictions than would be expected in a study population in the United States. Having a comparator arm in the study enables a fairer assessment of whether or not the rate of adverse events is “normal” or not, since to a reviewer unfamiliar with the study site, viewing the number of adverse events might otherwise lead to an erroneous – and negative – assessment of the vaccine’s safety.

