Starting in 2004, epidemiological studies have been conducted by the study team in the town of Americaninhas and surrounding areas in order to identify the populations at greatest risk for heavy hookworm infection and to conduct post-treatment hookworm re-infection studies in order to inform the sample size calculations for phase 1 and phase 2 studies in the region. These studies have been challenging because of a number of physical challenges including the isolation of the region, the hilly terrain, and the large distances between dwellings. Geographic Information System/Remote Sensing identified high levels of vegetation as a critical feature of the infection sites. Overall, the force of infection in Minas Gerais is high. It was estimated that post-treatment hookworm infection occurs in approximately 300 per 1,000 individuals per year, which represents a level of transmission that is comparable to other areas considered to have intense or high transmission, such as in East Africa. The overall prevalence of *N. americanus* hookworm infection is approximately 68 percent, with approximately one-half of the population also infected with *Ascaris lumbricoides* and with *Schistosoma mansoni*. As in other regions of the world, the prevalence of hookworm infection rises in the first 5 years of life when it reaches a plateau. In addition, the intensity of hookworm infection (as measured by fecal egg counts using the Kato-Katz technique) also rises until the age of 5 years and then remains high. A second increase in hookworm intensity occurs after the age of 50.

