#### Study Day 0 (Day of First Vaccination)

1. Verify that Informed Consent was obtained.
2. Verify that all applicable eligibility criteria have been met.

3. Perform abbreviated history (including concomitant medications) and physical exam, focusing on any acute complaints.
4. Obtain blood for hematology, biochemistry, anti-GST-1 and total IgE antibody ELISAs and cellular immunology assays.
5. For females, obtain a urine sample for hCG testing. Ensure that test is negative before proceeding; a positive test will exclude the volunteer from the trial.
6. Record vital signs (blood pressure, oral temperature, and heart rate).
7. Administer the vaccine.
8. Observe for at least 2 hours after vaccination to evaluate for immediate adverse reactions. During the 2-hour post-immunization wait period, study staff will discuss signs and symptoms of potential AEs.

#### Study Day 1

1. Perform basic history and physical exam (including injection site), emphasizing examination of any acute complaints.
2. Record vital signs.

#### Study Day 3 +/- 1

1. Perform basic history and physical exam (including injection site), emphasizing examination of any acute complaints.
2. Record vital signs.

#### Study Day 7 +/- 1

1. Perform basic history and physical exam (including injection site), emphasizing examination of any acute complaints.
2. Record vital signs.

#### Study Day 14 +/- 2

1. Perform basic history and physical exam (including injection site), emphasizing examination of any acute complaints.
2. Record vital signs.
3. Obtain blood for hematology, biochemistry, anti-GST-1 and total IgE antibody ELISAs, and cellular assays.

#### Study Day 28 +/- 4

1. Perform basic history and physical exam (including injection site), emphasizing examination of any acute complaints.
2. Record vital signs.
3. Obtain blood for anti-GST-1 and total IgE antibody ELISAs and cellular assays.

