## **7.8 Immunologic Testing**

### ***7.8.1 Anti-*Na*-GST-1 Antibody Assays***

Antibodies to *Na*-GST-1 will be measured in serum or plasma of study subjects using an indirect ELISA and/or a custom ImmunoCAP (Phadia, Inc.) assay. Antigen-specific IgG and IgE antibody levels will be measured by both methods at baseline and at several time-points post-vaccination; in addition, IgG subclasses will be measured by ELISA. For the ELISA method, microwell plates will be coated with purified recombinant *Na*-GST-1, blocked, and incubated with serial dilutions of a positive “standard reference serum” pool to generate a reference curve from which antibody levels of test sera can be interpolated. After washing, a horseradish peroxidase conjugated goat anti-human antibody will be added and incubated with plates,

washed again, incubated with a chromogenic substrate, and antibody levels measured on an ELISA plate reader.

Serum samples with anti-*Na*-GST-1 IgE results by ELISA that are greater than the reactivity limit will then be tested by the ImmunoCAP method. The ImmunoCAP method is considered to be the gold standard for measuring levels of antigen-specific IgE in serum. These tests will be performed at the Dermatology, Allergy, and Immunology Reference Laboratory of Johns Hopkins University (Baltimore, Maryland, US).

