The proportion of participants with at least one injection site AE will be compared by vaccine formulation and by dose cohort. The incidence of AEs will be compared across cohorts and not within cohorts. Therefore, the data for all participants who receive the hepatitis B vaccine (8 in total) will be summarized and compared to those who receive 10 µg *Na*-GST-1/Alhydrogel® (n=10), to those who receive 10 µg *Na*-GST-1/Alhydrogel®/GLA-AF, and so on. By merging the AE data of all participants who receive the same vaccine (hepatitis B, *Na*-GST-1/Alhydrogel®, or *Na*-GST-1/Alhydrogel®/GLA-AF), even if the individuals are not in the same cohort, the strength of the comparisons will be increased.

Laboratory results (hematological and clinical chemistry) will be examined for trends over time and any clinically significant values for individuals will be reported.

Secondary Objective 1: To determine the dose that generates the highest anti-*Na*-GST-1 IgG antibody response at Day 126, as determined by an indirect enzyme-linked immunosorbent assay (ELISA).

- a. The proportion of participants with detectable anti-*Na*-GST-1 responses will be summarized as a descriptive measure.
- b. Geometric mean antibody responses will be compared between vaccine formulation and dose groups. Comparisons between groups will be made by a one-way analysis of variance (ANOVA) with pair-wise comparisons between dose cohorts made by contrasts. Data from participants receiving the same vaccine (e.g., hepatitis B, *Na*-GST-1/Alhydrogel®, or *Na*-GST-1/Alhydrogel®/GLA-AF) will be combined across cohorts to increase the strength of the comparisons.

Secondary Objective 2: To assess and compare the duration of antibody response to *Na*-GST-1.

- a. Immunogenicity responses will be summarized by vaccine formulation and dose of *Na*-GST-1, over time.
- b. Individual responses will be described over time and stratified by *Na*-GST-1 formulation and by dose of *Na*-GST-1.

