- c. Antibody responses will be measured at Days 0, 14, 28, 56, 70, 84, 112, 126, 140, 200, 290, and 380. To exploit the multiple measures of antibody within each subject, a longitudinal model may be built (if possible) to describe the antibody response over time. The model will explore if there are any differences between *Na*-GST-1/Alhydrogel®, *Na*-GST-1/Alhydrogel®/GLA-AF and Butang®, and explore dose effects. As described for Secondary Objective 2, data from participants receiving the same vaccine will be combined across cohorts.

Secondary Objective 3: To perform exploratory studies of the cellular immune responses to the *Na*-GST-1 antigen both before and after immunization.

The following assays will be performed to assess the cellular immune responses to vaccination with *Na*-GST-1:

- a. Lymphocyte proliferative responses to *in vitro* stimulation with *Na*-GST-1.
- b. Cytokine and chemokine production *in vitro* in response to stimulation with *Na*-GST-1.
- c. Changes in *in vivo* PBMC subpopulations as determined by flow cytometry.

Summary statistics will be used to present these immunogenicity results. To assess the changes in lymphocyte proliferative responses over time, a generalized estimating equations model with robust standard errors will be constructed.

Should the study be terminated early (see **Section 8.5**), the investigative team will discuss with the SMC the reason for termination and determine which study questions can be addressed in an

unbiased manner with the available data. The available data will be analyzed and interpreted in light of early termination.

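### The one-way ANOVA of Day 126 IgG leaves out the Day 0 IgG collected on everyone, although Part II expects background antibody and its dose cohorts are not randomised against each other

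*Protocol*

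**What the plan says.** Section 10.1.1, Secondary Objective 1b, names the method for Day 126: "Comparisons between groups will be made by a one-way analysis of variance (ANOVA) with pair-wise comparisons between dose cohorts made by contrasts". Participants given the same vaccine are combined across cohorts, and no baseline covariate or Part term is named. Item (a) of the same objective adds a descriptive summary: "The proportion of participants with detectable anti-*Na*-GST-1 responses will be summarized as a descriptive measure".

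Day 0 antibody is available. The Day 0 visit in section 7.6 includes this step: "Obtain blood for hematology, biochemistry, anti-GST-1 and total IgE antibody ELISAs and cellular immunology assays". Section 7.8.1 states: "Antigen-specific IgG and IgE antibody levels will be measured by both methods at baseline and at several time-points post-vaccination". Under Secondary Objective 2 the schedule reads: "Antibody responses will be measured at Days 0, 14, 28, 56, 70, 84, 112, 126, 140, 200, 290, and 380".

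The protocol also says why baseline matters. Section 1.13.1 warns that in endemic areas "background immunity and natural exposure to hookworm infection may otherwise make it difficult to interpret immunogenicity data". Section 3 puts the site prevalence at this level: "hookworm infection is approximately 68 percent". Section 4.2 requires at least 4 recently infected people in each of Cohorts 7 to 12. Sections 4.1 and 4.3 enrol the dose cohorts consecutively; randomisation in Part II takes place only within a cohort.

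**The concern.** In a population repeatedly exposed to hookworm, part of the spread in Day 126 IgG may be antibody that was there before the first injection. An analysis that ignores Day 0 leaves that spread in the residual and widens every contrast.

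The second issue is bias. Doses are given to different cohorts, enrolled at different times, and no randomisation links them. Within a dose, 8 of the 10 Part II recipients of the Alhydrogel-only product come from one cohort and all 10 GLA-AF recipients from the next, so the formulation contrast is also largely between cohorts. The infected minimum of 4 per cohort is a floor, so the infected share may differ from cohort to cohort. If cohorts differ at Day 0, an unadjusted contrast takes in part of that difference.

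The Day 140 report, which contains the primary immunogenicity data, is the basis for deciding on testing in children and with which formulation (section 9.2.1).

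**Working it through.** **Inputs from the protocol.** In Part II each dose-formulation arm has 10 participants (8 + 2 for Alhydrogel only, 10 with GLA-AF). Part II has 66 participants in 7 groups (6 dose-formulation arms and Butang). Tests are two-sided at 5%. The protocol gives no SD, effect size, baseline IgG level or correlation for Day 126 IgG, and no power figure, so there is nothing to reproduce.

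**Assumptions, not from the protocol.** The correlation rho between log10 Day 0 and log10 Day 126 IgG in Part II is 0.3 to 0.6. For the power illustration, the log10 SD is 0.5 and the true difference 3-fold.

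**1. Noise.** Adjustment for Day 0 multiplies the residual variance by 1 − rho² and the standard error by √(1 − rho²).
- rho 0.3: √0.91 = 0.954, so the SE falls by about 5%. Equivalent sample size is 1/0.91 = 1.10 times.
- rho 0.6: √0.64 = 0.80, so the SE falls by 20%. Equivalent sample size is 1/0.64 = 1.56 times.

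**2. Power, 10 v 10.** Noncentral t gives 52% unadjusted, 56% with rho 0.3 and 64% with rho 0.5. A simulation of 20,000 trials per setting, which also allows for chance imbalance in the covariate, gives ANCOVA power of 54% and 63% at those correlations.

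**3. Cost when baseline is uninformative.** At rho = 0 the same simulation gives 52% for ANOVA and 50% for ANCOVA, a loss of about 2 points. That is for two groups alone. In a model over all of Part II the residual degrees of freedom go only from 66 − 7 = 59 to 58, so the loss should be smaller.

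**4. Bias from a systematic Day 0 difference.** If two cohorts differ at Day 0 by k baseline SDs, the unadjusted Day 126 contrast shifts by rho × k × SD. With no true vaccine difference, rho 0.5 and SD 0.5:

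| k | Shift (log10) | As a ratio | ANOVA rejects | ANCOVA rejects |
|---|---|---|---|---|
| 0 | 0 | 1.00 | 5% | 5% |
| 0.5 | 0.125 | 10^0.125 = 1.33 | 8% | 5% |
| 1.0 | 0.25 | 10^0.25 = 1.78 | 18% | 5% |

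The ANCOVA result assumes a linear relation on the log scale. It corrects for measured Day 0 IgG only, not for other differences between cohorts.

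**The case against.** *The detail belongs in the analysis plan.* Section 10.1.1 calls itself brief and defers to a detailed plan that is not at hand. That plan may add a covariate. But the protocol has already named a method, and that method by construction has no covariate, so this is a stated choice and not a missing detail.

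*The comparator is the protocol's remedy.* Section 1.13.1 raises background immunity in order to justify a control group. Butang recipients do show the average background. They number 6 (section 4.2), none of them in a GLA-AF cohort, and they do not adjust the contrasts among the Na-GST-1 arms.

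*Day 0 is used elsewhere.* Group and individual responses over time are firm commitments under Secondary Objective 2, so an imbalance would be visible. It would not be corrected, because the only model that could use Day 0 is optional and serves the duration objective.

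*The antigen may be hidden.* Sections 1.3 and 1.4 argue that natural infection hardly sensitises to it, which could make rho small. The data shown and the screening exclusion concern IgE, so they neither establish nor exclude background IgG.

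Three stronger readings are tempting, and the protocol does not support them:
- A reader might infer that a vaccine response is defined as detectable antibody. The text fixes no definition or cut-off; the proportion is descriptive and leads to no test.
- A reader might take a non-zero detectable rate in Butang recipients as a fault. It is the background that the comparator is there to reveal.
- A reader might count chance baseline imbalance as a further harm. For 10 v 6 its SD is √(1/10 + 1/6) = 0.52 baseline SDs, or 0.15 to 0.31 Day 126 SDs at rho 0.3 to 0.6. It is already contained in the ANOVA standard error. Only a systematic difference between cohorts is additional.

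**Conclusion.** The point holds in a limited form. The named Day 126 analysis discards a baseline measurement that is scheduled for everyone, in a population where the protocol expects background immunity and with dose groups that are not randomised against each other. The result is avoidable noise, and exposure to bias if cohorts differ systematically at Day 0.

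How much is lost cannot be settled from the protocol. The 5% to 20% reduction in SE rests on an assumed rho of 0.3 to 0.6. The bias figures rest on an assumed rho, SD and imbalance; nothing shows that such an imbalance will occur. A strong vaccine response could swamp the background. This is also a secondary objective in a trial that section 10.2 says is not powered for group differences, and the decision on testing in children rests on safety as well as immunogenicity. The change is worth making because it costs little, not because the planned analysis is invalid.

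**What to change.** In section 10.1.1, Secondary Objective 1b, replace the one-way ANOVA with an ANCOVA of log10 Day 126 IgG on arm (dose × formulation) and log10 Day 0 IgG. Fit it within Part, or with a Part term if the Parts are combined, and keep the planned contrasts. State in advance the value used for Day 0 results below the assay limit. Screening hookworm status can be an optional covariate in a Part II sensitivity analysis.

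Keep the detectable proportion under 1a as a description, and note that in Part II it may include antibody present before vaccination. Beside it, report the proportion with a pre-set rise over the participant's own Day 0 value, using the same rule for results below the limit.

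The cost is wording, to be settled before the Day 140 unblinding; no extra sampling or assay is needed. The downsides are one degree of freedom per covariate and dependence on the below-limit rule, which will matter if many Day 0 values are undetectable.

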| Study Design     | 
Two part study:
 
Part I: Open-label phase 1 trial in hookworm-naïve adults.
 

• Study site: Centro de Pesquisas René Rachou, Belo Horizonte, Brazil

• Number of participants: 36 in 6 groups of 6. The first, third, and fifth groups will receive Na-GST-1/Alhydrogel® and the second, fourth, and sixth will receive Na-GST-1/Alhydrogel® plus GLA-AF. Cohorts will be enrolled consecutively, with the first and second receiving 10 µg Na-GST-1, the third and fourth 30 µg Na-GST-1, and the fifth and sixth 100 µg Na-GST-1.

 
Part II: Double-blind, randomized, controlled dose-escalation phase 1 clinical trial in hookworm exposed adults.
 

• Study site: Americaninhas, Minas Gerais, Brazil.

• Number of participants: 66 in 6 groups, randomized to receive either Na-GST-1/Alhydrogel®, Na-GST-1/Alhydrogel®/GLA-AF, or Butang® hepatitis B vaccine.

• Immunization schedule: Study days 0, 56 and 112.

• Route: IM in the deltoid muscle.

• Doses of Na-GST-1 to be tested: 10, 30 and 100 µg

• Doses of Alhydrogel®: 80, 240 and 800 µg for the 10, 30 and 100 µg doses of Na-GST-1.

• Dose of GLA-AF: 2.5 µg.

• Study duration: 24 months; each participant will be followed for a total of 16 months.

 |

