### 4.3 Group Allocation

Dose cohorts will be enrolled consecutively. In **Part I** of the study, within Cohort 1 all participants will receive the 10 µg dose of *Na*-GST-1/Alhydrogel®; within Cohort 2, all will receive 10 µg of *Na*-GST-1/Alhydrogel®/GLA-AF, and so on. In **Part II** of the study, within Cohorts 7, 9 and 11 of 10 participants, 8 will be randomly assigned to receive *Na*-GST-1/Alhydrogel® and 2 to receive Butang® (see **Section 7.3**). Within Cohort 7, Cohort 9, and Cohort 11, those randomized to receive *Na*-GST-1/Alhydrogel® will receive a dose containing 10 µg, 30 µg and 100 µg of *Na*-GST-1, respectively. Also in Part II of the study, within Cohorts 8, 10, and 12 of 12 participants, 2 will be randomly assigned to receive *Na*-GST-1/Alhydrogel® and 10 to receive *Na*-GST-1/Alhydrogel®/GLA-AF. Within Cohorts 8, Cohort 10, and Cohort 12, participants will receive a dose containing 10 µg, 30 µg and 100 µg of *Na*-GST-1, respectively.

In both **Part I** and **Part II** of the study, 1 or 2 additional eligible volunteers above the number to be enrolled in a given cohort may be scheduled for a Day 0 visit, if possible. On the day of first vaccination, the first volunteers who arrive at the study clinic will be evaluated for continued eligibility and vaccinated in the order that they arrive; the additional eligible volunteers will be kept as alternates if some of the first arrivals cannot be vaccinated on the day of first vaccination (i.e., due to pregnancy, withdrawal of consent, etc.). If the alternates are not vaccinated, they will be invited to participate as members of the next dose cohort. Those alternates for the final cohorts in both Part I and Part II who are not vaccinated and therefore not enrolled in the study, will be offered vaccination with a non-study, licensed vaccine such as the tetanus toxoid or influenza vaccine.

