##### ***10.1.1 Description of the Statistical Methods to Be Employed***

The purpose of this trial is to estimate AE rates and patterns of immune response as well as to compare these rates and patterns between the investigational and comparator vaccines, in different doses of the *Na*-GST-1 formulations.

This section briefly describes the statistical methods to be used; a detailed analytical plan will fully describe the methods. The analytical plan will discuss the planned approaches to missing data. Deviations from the original analytical plan will be thoroughly documented and reported to the Sponsor.

Descriptive and hypothesis-testing approaches will be used to meet the protocol objectives as stated in **Section 2.0**. Estimates will be presented with their 95% confidence intervals. Formal statistical tests, as outlined below, will be used to compare doses. No formal adjustments for multiple comparisons will be made. Statistical tests will use a two-sided significance level of 5%.

**Primary Objective:** To estimate the frequency of vaccine-related AEs, graded by severity, for each dose and formulation of *Na*-GST-1.

AEs will be coded according to Medical Dictionary of Regulatory Activities (MedDRA™) preferred terms. The frequency, severity, and relationship of AEs for each vaccine formulation and dose cohort will be presented in tabular form using the MedDRA™ coded term and organized by MedDRA™ System, Organ, and Class (SOC) designations.

- The frequency of immediate, systemic, and local injection site AEs will be summarized by SOC and preferred term.
- A line listing of each clinical and laboratory AE classified as immediate (within the first 2 hours), systemic, and local will be displayed in tables stratified by vaccine allocation and dose cohort.
- AEs will be summarized by severity and relationship to vaccine formulation by individuals and dose of *Na*-GST-1.
- The frequency of vaccine-related SAEs will be tallied as well as summarized by body system, by vaccine formulation and dose cohort.

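### If the GEE's robust standard errors are the usual uncorrected ones with a normal reference, nominal 5% tests of lymphocyte proliferation run at about 7–13% in dose-level groups and about 10–11% against the 6 Butang recipients (minor; exploratory objective)

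*Protocol*

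**What the plan says.** Protocol Section 10.1.1 names one inferential model for the cellular assays. For change in lymphocyte proliferation over time, "a generalized estimating equations model with robust standard errors will be constructed". The other cellular results are to be summarised descriptively.

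The same section presents estimates with 95% confidence intervals and sets the test level ("Statistical tests will use a two-sided significance level of 5" per cent). It adds that "No formal adjustments for multiple comparisons will be made".

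Two statements limit how much can be read into the GEE sentence. The section calls itself an outline: "This section briefly describes the statistical methods to be used; a detailed analytical plan will fully describe the methods". The objective is labelled exploratory: "To perform exploratory studies of the cellular immune responses to the *Na*-GST-1 antigen both before and after immunization".

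Group sizes come from the design. Part I enrols "36 in 6 groups of 6". In each of Cohorts 7, 9 and 11, "8 will be randomly assigned to receive *Na*-GST-1/Alhydrogel ® and 2 to receive Butang". In each of Cohorts 8, 10 and 12, 2 receive the Alhydrogel formulation and 10 the GLA-AF formulation (Section 4.3). Section 4.2 gives 6 Butang recipients among 102 participants.

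**The concern.** The standard sandwich variance is a large-sample estimator. In a small group it is biased downward, because it averages squared residuals without allowing for the estimated mean. Referring the statistic to the normal distribution also ignores the uncertainty in the variance itself. Both errors make intervals too short and rejections too frequent.

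This trial has few participants per dose and formulation, and very few on the comparator. Robust standard errors in their usual software form may therefore miss the plan's own 5% level and 95% coverage. The error is towards declaring cellular responses, or differences from Butang, that are not there. Up to 11 assay visits (Days 0 to 290 in Appendix B) and unadjusted multiple comparisons give it many chances to appear.

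**Working it through.** The plan gives no operating characteristic for this model, so there is no figure to reproduce except the chosen 5%. The check is whether that level is met.

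**Inputs**
- Level: two-sided 5%, critical value 1.96 under a normal reference (Section 10.1.1 for the level; the normal reference is an assumption).
- Part I: 6 per dose and formulation (Table 1).
- Part II: 8 + 2 = 10 per dose on Alhydrogel, and 10 per dose on GLA-AF (Section 4.3).
- Both Parts merged: 6 + 8 + 2 = 16 and 6 + 10 = 16 per dose.
- Butang: 3 cohorts × 2 = 6, as in Table 1 and Section 4.2. The safety paragraph of Section 10.1.1 counts 8, which does not match the allocation; 6 is used here.
- By vaccine alone: 48, 48 and 6, total 102.
- Assumptions: normal changes, complete data, equal variances.

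**Change within one group.** Let D be each participant's change (or slope), with n participants and sample variance s². The GEE estimate is the mean of D. Its uncorrected sandwich variance is Σ(D − mean)²/n² = [(n−1)/n] × s²/n. The Wald statistic is therefore the ordinary t statistic times √[n/(n−1)], and

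true size = 2 × P(t with n−1 df > 1.96 × √[(n−1)/n]).

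| n | 1.96 × √[(n−1)/n] | df | true size |
|---|---|---|---|
| 6 | 1.789 | 5 | 13.4% |
| 8 | 1.833 | 7 | 10.9% |
| 10 | 1.859 | 9 | 9.6% |
| 16 | 1.898 | 15 | 7.7% |
| 48 | 1.939 | 47 | 5.85% |
| 102 | – | 101 | 5.4% |

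At n = 6 a nominal 95% interval covers 100 − 13.4 = 86.6%. Its width relative to the t interval is 1.789/2.571 = 0.70, so it is 30% narrower.

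**Difference in change between two groups.** The variance is the sum of two terms of the form above. Sizes are from 400,000 simulated data sets per row (Monte Carlo error about 0.05 points). The last column uses the unbiased variance with Satterthwaite degrees of freedom.

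| groups | uncorrected, normal | corrected, t |
|---|---|---|
| 6 v 6 | 10.4% | 4.6% |
| 6 v 10 | 9.5% | 4.9% |
| 6 v 16 | 9.7% | 5.2% |
| 10 v 10 | 7.9% | 4.8% |
| 16 v 16 | 6.7% | 4.9% |
| 6 v 48 | 11.3% | 5.5% |
| 48 v 48 | 5.5% | 5.0% |

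Equal groups have a closed form: 2 × P(t with 2n−2 df > 1.96 × √[(n−1)/n]). It gives 10.4% for n = 6 and 6.7% for n = 16, which agrees.

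**Check with fitted GEEs.** These used the 11 assay visits, a random intercept and slope, an independence working correlation and 2,500 runs. With uncorrected robust errors and 1.96, a slope in a group of 6 was rejected in 12.8% of runs and in a group of 16 in 8.5%. Slope differences gave 9.8% (6 v 16) and 6.5% (16 v 16). These agree with the calculations above to within simulation error.

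**Does correcting the variance alone suffice?** No. With the unbiased variance but still 1.96, one-group change runs at 10.7% for n = 6 and 6.9% for n = 16. In the fitted GEEs, a bias-reduced covariance with 1.96 left one-group slopes at 8.2% and 6.4%. The unbiased variance with t on n−1 degrees of freedom gives exactly 5%.

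**The case against.** The strongest reply is that the protocol does not specify the faulty version. It says robust standard errors; it does not say uncorrected ones and does not name a normal reference. A bias-corrected sandwich with a t reference is also a GEE with robust standard errors, so it would satisfy the sentence as written. Such detail often belongs in the analytical plan, which the section announces and which is not available here. This stands, and it is why the point is conditional.

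The second reply is that no grouping is fixed for this model. For the safety and antibody analyses, Section 10.1.1 combines recipients of the same vaccine across cohorts. Carried over literally, that gives 48, 48 and 6, and at 48 the excess is under one percentage point. This also stands, with one exception: pooling the hookworm vaccine arms does nothing for the comparator. A contrast of 6 with 48 is worse (11.3%) than 6 with 6 (10.4%), because the variance is dominated by the 6. Since the section states a purpose of comparing immune-response patterns with the comparator, that contrast is a natural one.

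The third reply is consequence. The objective is exploratory, Section 10.2 says the trial is not powered for group differences, and the model covers one assay. The decision on testing in children uses safety and primary immunogenicity data (Section 9.2.1), and the primary immunological result is IgG by ELISA (Section 8.10). This stands in full. Low power does not excuse an inflated error rate, but little hangs on it here.

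A reader might infer that the protocol commits to an inflated test, or that every group is affected. The text supports neither.

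**Conclusion.** The point holds conditionally and is minor. In its usual form, uncorrected and referred to the normal distribution, the named method misses the plan's own 5% level at the design's dose-level and comparator sizes:

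- about 8–13% for change within a dose-and-formulation group of 6 to 16;
- about 7–10% for contrasts between such groups;
- about 10–11% for any contrast with the 6 Butang recipients, pooled or not;
- about 5.5–6% for vaccine-level groups of 48.

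The figures rest on normal changes and complete data. The outcome is a stimulation index whose analysis scale is not stated; skewness, unequal variances or dropout would move them. For example, if the 6 Butang recipients had twice the standard deviation of a group of 16, the size would be 12.0%; with half of it, 8.0%.

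No stated decision of the trial is affected.

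**What to change.** Under Secondary Objective 3 in Section 10.1.1, carried into the analytical plan, state one of the following:

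- a GEE with a bias-corrected sandwich (for example Kauermann-Carroll or Mancl-DeRouen) and a t reference on between-subject, Satterthwaite-type degrees of freedom; or
- a mixed model on the log stimulation index with Kenward-Roger degrees of freedom.

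The t reference is an essential part of the first option, since variance correction alone leaves the small groups inflated. Mancl-DeRouen corrects more strongly, so with a t reference it errs somewhat on the conservative side. The same sentence should say which groups are tested and whether the two Parts are merged, because the size of the problem depends on it. If the analytical plan already specifies this, only a cross-reference is needed.

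The cost is one sentence and a software option, with no change to data collection or sample size. Intervals become wider, most visibly for Part I groups and Butang.
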